#### Recruitment of patients

Patients are recruited in three centers: The University Hospital Cologne/ CIO Cologne Bonn, the St.-Antonius-Hospital in Eschweiler, and the Oncological Practice at the Sachsenring in Cologne. The numbers of patients are based on the average number of patients in the respective centers per year over the past 2 years, considering denial or drop-out and applied to the recruitment period.

#### Data management and analyses

Data entry is continuously monitored by a data manager (TN) and will be analyzed by a statistician (ML). For the primary endpoint incident CIPN, censoring will be taken into account by using log-rank tests, and multivariable Cox proportional hazard regression models will be used to test for differences between groups and to estimate treatment effects. For categorical secondary endpoints, Fisher’s exact test and Wilcoxon signed-rank tests and multivariable logistic regression models will be performed. For continuous outcomes (including scores derived from self-report questionnaires), t-tests and multivariable linear or median regression models will be used. Multivariable models will adjust for study center, type of chemotherapy, type of cancer, gender, and age. Intention-to-treat analyses will be conducted based on complete cases and on multiply imputed data using a conditional imputation [48].

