### Experimental design

The study follows a prospective, randomized controlled design, allocating patients to three groups: an intervention group receiving SMT, an additional intervention group receiving WBV, and a control group (Fig. 1). Patients in the two intervention groups receive a defined exercise program twice a week in addition to treatment as usual (TAU). Patients in the control group receive TAU and are given the opportunity to participate in the preferred intervention after completion of the study. The interventions and assessments take place at the respective centers.

Data is assessed at 3 to 5 measuring time points, depending on the length of medical therapy and a potential incidence of CIPN (Fig. 2 and Fig. 3). The baseline assessment (T0) is performed prior to the first cycle of chemotherapy. All patients are re-assessed after three months (T1). For most patients, this is simultaneously the post-therapy measurement (Tp) (Fig.2), while for patients who are treated for more than three months it represents an interim assessment (T1) (Fig.3), in order to ensure comparability regardless of the entity. These patients have an additional assessment upon completion of their medical therapy (~6 months). The follow-up measurement is performed three months after completion of chemotherapy (T2) in order to compensate for any potential coasting effects. Each assessment has a duration of 90 min at most. To ensure the detection of CIPN, patients are informed about possible symptoms of CIPN and asked to report back to the study coordinators immediately. Furthermore, patients are regularly asked for potential symptoms by their physicians. Additionally, a short neurological test battery is performed every 6 weeks. Sports therapists will be blinded and must not ask patients about CIPN symptoms during the interventions in order to obtain comparability with the control group. In case a CIPN is neurologically confirmed, patients are also tested at this time point (Ti).

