#### Nerve conduction studies

For nerve conduction studies, motor and sensory nerves are assessed. Compound muscle action potentials (CMAP), distal motor latency, conduction velocity, and F-waves are obtained from the tibial nerve. The tibial nerve is stimulated at the ankle and popliteal fosse. Antidromic sensory nerve conduction studies are performed in the sural nerve. Sensory nerve action potentials (SNAPs) are recorded from the lateral malleolus with surface electrodes. Skin temperature is monitored and maintained above 32 °C using a heater if necessary.

We furthermore conduct a standardized neurological clinical test battery that is a feasible assessment method for oncological patients in order to check for first neuropathic symptoms. It is used as a pretest to screen for CIPN related symptoms. Should one of the components show irregularities, a neuroelectrography is required in order to detect and document a possible CIPN.

The test battery contains the following assessments:**Peripheral deep sensitivity** is evaluated by the use of a Rydel-Seiffer tuning fork (128 Hz) with a scale from 0 to 8. Due to age related neural deconditioning, values ≤4 are pathological for patients ≥60 years old, while for patients under 60 years old, ≤5 is regarded as pathological [34].**The Reflex action** of the Achilles- as well as the patellar tendon is assessed with a reflex hammer and graded on a 3-point scale (1 = agile, 2 = weak, 3 = missing).**Sense of position** is assessed by asking patients if they can recognize a change of position in their first toe, with their eyes closed.**Perception of touch** is evaluated by symmetrically stroking the outsides of the patients’ legs and feet in order to detect reduced or altered sensation due to demyelination or axonal degeneration [30, 35].**The strength of the lower leg muscles** is assessed by requesting the patient to actively move their legs against the resistance of the examiner’s arm. The examiner then grades the strength on a six-point scale (0 = no activity, 1 = visual contraction without motor effect, 2 = movement under elimination of gravity, 3 = movement under gravity, 4 = movement against slight resistance 5 = normal force).

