### Statistical procedures and sample size estimation

Central computerized randomisation (RITA) using a modified minimization procedure with stochastic component according to Pocock and Simon is performed [45]: intervention 1: intervention 2:control = 1:1:1, stratified by study center and type of therapy (Oxaliplatin, Vinca-alkaloids). In trials under similar conditions, a balanced randomization has been achieved using this algorithm [14].

Sample size calculation is based on the primary endpoint incident CIPN. Power calculation is based on the following scenario: The assumed incidence rate with TAU is 90%, which was informed by a review of the literature. In both intervention groups, we assumed an incidence rate of 75%. The effect size corresponds to a relative risk of about 0.60, which is a clinically meaningful effect size. Using the log-rank test (1-β = 0.8, two-sided α = 0.05), we need a total of 196 evaluable patients, 65 per group [46, 47]. We anticipate a drop-out rate of 10%, yielding a total of 236 patients to be recruited for this study, 79 per group. This calculation is conservative as we may achieve additional power performing the final analysis using a multivariable Cox proportional hazards regression model adjusting for study center, type of chemotherapy, type of cancer, gender, and age.

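### The Wilcoxon signed-rank test listed for categorical secondary endpoints is a paired test and cannot compare the independent randomised arms; an unpaired rank test should be named

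*Protocol article*

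**What the plan says.** The secondary analyses are set out in the protocol article under *Data management and analyses*. For categorical outcomes the list opens with Fisher's exact test and continues: "Wilcoxon signed-rank tests and multivariable logistic regression models will be performed". That sentence does not say which comparison the signed-rank test serves. An explicit between-group purpose appears only for the primary endpoint, where "multivariable Cox proportional hazard regression models will be used to test for differences between groups and to estimate treatment effects".

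The design is described under *Experimental design* as a "prospective, randomized controlled design, allocating patients to three groups". The allocation under *Statistical procedures and sample size estimation* is "intervention 1: intervention 2:control = 1:1:1, stratified by study center and type of therapy". Neither section mentions matched pairs or crossover.

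Repeated measurement exists within patients: "Data is assessed at 3 to 5 measuring time points, depending on the length of medical therapy and a potential incidence of CIPN". The clinical test battery contains ordered grades. Tendon reflexes are "graded on a 3-point scale (1 = agile, 2 = weak, 3 = missing"), and for leg muscles "The examiner then grades the strength on a six-point scale". The tuning fork is read on a 0 to 8 scale.

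**The concern.** The signed-rank test is a one-sample test on within-patient differences. Its neighbours in the sentence, Fisher's exact test and multivariable logistic regression, are the usual tools for comparing independent groups, so the likeliest explanation is a slip for the Wilcoxon rank-sum test. As printed, the sentence offers an analyst one of two things: a test that has no pairs to work on between arms, or a within-arm test of change over time whose purpose is not stated.

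At stake is how ordered secondary outcomes are reported. Three methods are listed with no order of precedence. A within-arm signed-rank p-value could therefore be presented as a prespecified result although it does not address the randomised comparison, and no unpaired rank test is named to take its place.

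**Working it through.** No figure in the protocol depends on this test, so there is nothing to reproduce. The check is of the test's data requirement against the design, followed by an illustration.

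**1. What the test needs.** For patient i with scores X_i (first visit) and Y_i (later visit), form D_i = Y_i − X_i, rank the non-zero |D_i|, and sum the ranks of the positive D_i. The null hypothesis is that D is symmetric about zero. Every term requires X and Y from the same unit.

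**2. What the design supplies.** The protocol gives 196 evaluable patients, about 65 per group (for example 66 + 65 + 65 = 196). Patients in different arms are different people, so no D_i can be formed across arms. Given two independent arms of 66 and 65, the standard routine returns an error rather than a p-value. The only pairs are repeat visits of one patient.

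**3. What a within-arm test answers.** It asks whether D is centred on zero in that arm. The treatment question is whether the distribution of D, or of the follow-up score, differs between an intervention arm and TAU. Equal worsening in both arms makes the first null false and leaves the second true.

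**4. Illustration under assumed inputs.** Only the 65 per arm comes from the protocol. The rest is assumed: baseline N(6.5, 1); follow-up = baseline − d + N(0, 1); both rounded and limited to 0-8; the same d in both arms, so there is no treatment effect; two-sided 5% level; 1,000 to 2,000 simulated trials per setting.

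| Worsening d in both arms | Within-arm signed-rank rejects |
|---|---|
| 0.1 | about 25% |
| 0.25 | about 65% |
| 0.5 | about 98% |

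The between-arm rank-sum test on change stayed near its nominal 5% throughout (4.3% to 7.0% across runs, the spread being simulation error). The d values apply before rounding and capping; the ceiling at 8 adds a little further recorded decline.

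**5. One arm significant, the other not.** With independent arms and within-arm rejection probability p, exactly one of two arms is significant with probability 2p(1 − p):
- p = 0.25: 2 × 0.25 × 0.75 = 0.375
- p = 0.65: 2 × 0.65 × 0.35 = 0.455, matching about 45% in simulation
- p = 0.98: 2 × 0.98 × 0.02 = 0.039

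**6. A second scale.** On a 3-point grade (assumed baseline 60/30/10%, assumed 20% chance of worsening by one grade in both arms, 65 per arm, 2,000 runs), the within-arm test rejected in 99.9% of runs and the between-arm rank-sum test on change in 4.9%.

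**The case against.** The strongest reply is that the protocol never says this test compares arms. Patients are measured several times, and within-patient change from baseline is a legitimate thing to describe. That stands as a possible reading. But the purpose is not stated, and such a test would still not estimate the effect of randomised treatment.

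Second, valid between-arm methods are already in the same sentence: Fisher's exact test, and logistic regression adjusted for centre, chemotherapy, cancer type, gender and age. This stands in full and limits the consequence.

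Third, it is not certain which outcomes the test was meant for. The reflex, strength and tuning-fork grades are described under the primary-endpoint assessment, as a screen for CIPN. The abstract lists sensory and motor nerve-fibre function as secondary but does not say that these grades measure it. The 0-8 tuning-fork score might also be handled as continuous, or split at the protocol's own pathological cut-offs. This stands too, so the grades serve here as examples of ordered outcomes and not as a confirmed list.

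Some stronger readings are tempting but unsupported:
- A reader might infer that the trial will claim benefit because change is significant in one arm and not in another. The document nowhere proposes that inference; it is only a possible misuse.
- A reader might infer that the test must be significant because chemotherapy worsens the scores. The document gives no expected decline on these scales, and the rejection rate runs from about 25% to 98% over the assumed range.
- A reader might infer that ordered scores will otherwise be dichotomised. The text does not say so, and logistic regression can include ordinal models.

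**Conclusion.** The point holds as an error in the named test, of limited reach. A paired test is listed for a parallel-group trial, it cannot compare SMT or WBV with TAU, and no unpaired rank test is named for ordered outcomes. This is a procedure stated wrongly in the text, not detail deferred to a statistical analysis plan.

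The reach is confined to categorical secondary endpoints, and among those to the unadjusted rank test. The primary analysis and the sample size do not depend on it. It should be corrected before analysis, but it does not threaten the trial's main conclusion. The paired-versus-unpaired argument needs no assumption beyond the stated design; the simulated percentages rest wholly on the assumed score distribution and amount of worsening.

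**What to change.** In *Data management and analyses*, replace the signed-rank test by the Wilcoxon rank-sum (Mann-Whitney) test for ordered categorical secondary endpoints. Compare each intervention with TAU, on the follow-up score or on change from T0, and use Kruskal-Wallis if a single three-arm test is wanted. Fisher's exact test can stay for binary and unordered outcomes, and the adjusted logistic models can stay as they are.

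If within-arm signed-rank tests are wanted, say so separately, label them descriptive, and state that they will not be used as evidence of a treatment effect.

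Stratifying the rank test by type of chemotherapy, or using a proportional-odds model with the T0 score as covariate, would be reasonable refinements but is not needed to correct the error.

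The cost is one sentence in the protocol or the statistical analysis plan, with no change to data collection or sample size.

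### Continuous secondary outcomes are measured at baseline and at least twice more, but the named analyses use neither the repeated values nor the baseline value, so precision is lost

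*Protocol article*

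**What the plan says.** The section Data management and analyses says that for continuous outcomes, including questionnaire scores, "t-tests and multivariable linear or median regression models will be used". The adjustment set follows: "Multivariable models will adjust for study center, type of chemotherapy, type of cancer, gender, and age". It contains no baseline value of the outcome, no visit and no patient term. On missing data: "Intention-to-treat analyses will be conducted based on complete cases and on multiply imputed data using a conditional imputation".

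The Experimental design section describes repeated measurement: "Data is assessed at 3 to 5 measuring time points, depending on the length of medical therapy and a potential incidence of CIPN". On the three-month visit T1 it says: "For most patients, this is simultaneously the post-therapy measurement (Tp". Patients treated for longer have T1 as an interim visit and a separate Tp at about six months. On the last visit: "The follow-up measurement is performed three months after completion of chemotherapy (T2".

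Table 1 places nerve conduction, postural control and all questionnaires at T0, T1, Tp and T2, and also at Ti if CIPN occurs.

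**The concern.** A t-test, a linear regression or a median regression takes one value per patient. Every patient is due to give a baseline value and at least two later values for each outcome. Because the article names both the method and the covariates, an analysis plan that follows it would carry single-value methods over to repeated data.

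What is at stake is precision on pain, nerve function, symptoms, quality of life and physical activity. The trial was sized on incident CIPN alone ("we need a total of 196 evaluable patients, 65 per group"), so these outcomes have no power target of their own. The measurements that could sharpen them are already being collected.

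**Working it through.** The article gives no standard deviation, effect size, correlation or power for any continuous secondary outcome, so it has no figure to reproduce. The rest is illustration under stated assumptions.

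**Inputs from the article.** 236 to be recruited, 79 per arm; 196 evaluable, 65 per arm; stated drop-out 10%. The loss implied by the two totals is 1 − 196/236 = 17%.

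**Assumptions.** Outcome variance 1 at every visit; the same correlation ρ between any two visits; 8% lost by end of therapy and 17% by T2, with no return after loss. So n₁ = 0.92n and n₂ = 0.83n, where n = 79.

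**1. Average over end of therapy and T2 against a T2 t-test, no baseline covariate.**
- T2 mean per arm: variance 1/(0.83n).
- Repeated-measures estimate of the two-visit average: variance ¼[(1+ρ)²/0.92 + (1−ρ²)/0.83]/n.
- The ratio is the second divided by the first. For ρ = 0.5: ¼(2.25/0.92 + 0.75/0.83) × 0.83 = 0.695.

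| ρ | Variance ratio | Reduction |
|---|---|---|
| 0.5 | 0.695 | 30.5% |
| 0.6 | 0.737 | 26.3% |
| 0.7 | 0.779 | 22.1% |

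For an assumed effect of 0.4 SD at both visits, the T2 standard error is √(2/(0.83 × 79)) = 0.175. Power is Φ(0.4/0.175 − 1.96), about 63%. For the average, the standard errors at ρ = 0.5 and 0.7 are 0.146 and 0.154, and power is 78% and 74%.

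**2. The T2 difference itself.** Here the question stays the same, and the model gains only by borrowing from patients seen at end of therapy but not at T2. The reduction is ρ²(1 − 0.83/0.92) = 0.098ρ², which is 2.4%, 3.5% and 4.8% for ρ = 0.5, 0.6 and 0.7.

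**3. Sensitivity to the loss assumed.** With the stated 10% by T2 instead of 17%, and 8% still lost by end of therapy, replace 0.83 by 0.90. The ratio in step 1 becomes 0.738 to 0.834 (reduction 17 to 26%). The gain in step 2 falls to ρ²(1 − 0.90/0.92) = 0.5 to 1.1%.

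**4. The baseline value.** With 65 per arm and complete data, the variance relative to a one-visit t-test is 1 − ρ² after baseline adjustment at one visit, and (1+ρ)/2 − ρ² for a baseline-adjusted mean of two visits. The difference detectable with 80% power is 2.80 × √(2v/65) SD, where v is that relative variance.

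| ρ | One visit, t-test | One visit, baseline-adjusted | Two-visit mean, baseline-adjusted |
|---|---|---|---|
| 0.3 | 1 (0.49 SD) | 0.91 (0.47 SD) | 0.56 (0.37 SD) |
| 0.5 | 1 (0.49 SD) | 0.75 (0.43 SD) | 0.50 (0.35 SD) |
| 0.7 | 1 (0.49 SD) | 0.51 (0.35 SD) | 0.36 (0.30 SD) |

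For one named visit, the baseline value gives more than the repeated-measures structure does, and it leaves the question unchanged. Its gain depends wholly on how well the pre-chemotherapy value predicts the later one, which the article does not say.

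**The case against.** A t-test or regression at one named visit is valid in a randomised trial, and preferring a longitudinal model is a matter of efficiency. That stands: nothing here is biased. The named methods would also fit a change score or a per-patient summary, and the choice of visit may sit in an analysis plan that is not shown. That stands too, so the unnamed visit is not held against the article. What remains is that a method and a covariate list are stated, and neither uses the repetition or the baseline value.

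Much of the 22 to 30% comes from changing the question from T2 alone to an average. This is correct, and the T2-only gain is therefore given separately. An equal effect at both visits is also not assured: training runs during therapy, whereas T2 comes three months after chemotherapy and is there to allow for coasting.

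A reader might infer two stronger points that the documents do not support.
- *The same data are tested twice, as T1 and as Tp.* No section says that both are tested. The count of three to five time points treats T1 and Tp as one measurement for three-month regimens.
- *Patients without T2 contribute nothing.* The article plans multiple imputation beside the complete-case analysis, and imputation can use their end-of-therapy values.

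**Conclusion.** The point holds as a loss of precision on secondary outcomes. It is not an error of validity, and it does not touch the primary endpoint. Its size cannot be read from the documents. The figures rest on assumed correlations, an assumed 8% early loss and a 17% loss taken from the two sample-size totals; the stated 10% drop-out gives smaller gains. The gain is material if an average over end of therapy and T2 is of interest and the effect is similar at both. It is small for the T2 difference alone, apart from what baseline adjustment adds. The change is worth making because it uses data already collected.

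**What to change.** For each continuous outcome, fit one mixed model for repeated measures with arm, visit, arm-by-visit interaction, the listed covariates and the outcome's baseline value, allowing for within-patient correlation.

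Define visits so that each measurement enters once:
- end of therapy for all patients (Tp, which is T1 in three-month regimens);
- T2 for all patients;
- the separate T1 of longer regimens as an additional interim visit, whose arm difference then describes those regimens only.

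Report the visit-specific arm differences, with the average over end of therapy and T2 as a summary. Keep median regression as a sensitivity analysis for skewed scores.

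The cost is a few sentences in the analysis plan and slightly more programming; no extra data are needed. The downside is that an average may blend effects that differ during and after therapy, so it should not be reported without the visit-specific estimates.

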## Methods/design

### Study participants and recruitment

We plan to enrol 236 newly diagnosed haematological/oncological patients who are scheduled to receive chemotherapy containing either oxaliplatin or a vinca-alkaloid, aged ≥18 years, with the mental and physical ability to provide signed informed consent and participate in the study. Patients are recruited at three participating centres: The University Hospital of Cologne, the St. Antonius Hospital in Eschweiler and the joint practice for oncology and hematology at the Sachsenring in Cologne. Exclusion criteria is a pre-existing neuropathy of other cause. Therefore, patients will be assessed clinically for signs of neuropathy and will undergo nerve conduction studies prior to randomization. Neuropathy will be defined electrophysiologically as CMAP amplitude below 5 mV, SNAP amplitude below 5 μV, and nerve conduction velocity below 40 m/s of tibial or sural nerve). Further exclusion criteria are previous therapies containing neurotoxic agents, any contraindication for whole body vibration (instable bone metastases, acute leg thrombosis, a fracture in the lower extremities in the past 2 years, foot ulcers, artificial hips or other osteosynthesis), and myocardial infarction, angina pectoris or heart disease (NYHA III-IV) within the past six months.

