### Assessment - primary endpoint

In order to assess the time to incidence of a neurologically confirmed CIPN, a comprehensive **Neurophysiological assessment** that includes the entire symptom pattern of CIPN, is necessary (Table 1):

**Table 1 Tab1:** Flow-chart of assessments

		Baseline T0	T1	Tp	T2	Ti	Status measurement
Time points		Prior to first cycle of therapy	After 3 months	After medical therapy	3 month follow-up	Incidence CIPN	every 6 weeks
Intervention	Training	2 x per week throughout entire medical therapy			Patients offered to continue		
Anamnesis I	Entity, stadium, pre-treatment, pre-diseases, allergies, planed therapy, neurological anamnesis, CIPN relevant medication, social anamnesis	X					
Anamnesis II	Begin of CIPN Symptoms, reception of planed therapy. Amount of cycles, potential change of medication or therapy, CIPN relevant medication			X	X	X	
Anamnesis III	Reception of CIPN relevant medication, therapy of CIPN			Only CG	Only CG	Only CG	
Neurological assessment	Neuroelectrography (NCV, Amp)	X	X	X	X	X	
	Neurological clinical tests battery	X	X	X	X	X	X
Performance status	Static and dynamic postural control	X	X	X	X	X	
Questionnaires	Subjective reduction of symptoms (FACT/GOG-Ntx / EORTC CIPN 20) Quality of life (EORTC QLQ-C 30) Neuropathic pain (PainDETECT and VAS) Level of physical activity (FFKA)	X	X	X	X	X	

*CIPN* Chemotherapy-induced peripheral neuropathy, *CG* control group, *NC*V nerve conduction velocity, *Amp* amplitude, *VAS* visual analogue scale

Nerve conduction studies are performed by trained, certified and blinded examiners. For patients of the University Hospital Cologne as well as the joint practice at Sachsenring, neurophysiological assessments are performed in the Electrophysiology Laboratory of the Department of Neurology, University Hospital Cologne. Patients in Eschweiler are seen by a local neurologist. Assessment methods are standardized and aligned among the investigators. Furthermore, patients are asked not to mention the arm they are participating in to the investigators. Examiners are trained by a gold-standard examiner using a standard operating procedure and certified prior to the study.

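### The covariate list for the continuous secondary endpoints omits the outcome's own T0 value, which costs precision that the collected data could supply

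*Protocol article*

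**What the plan says.** The section on data management and analyses states that for continuous outcomes, including questionnaire scores, "t-tests and multivariable linear or median regression models will be used". It then gives a single list for all regression models: "Multivariable models will adjust for study center, type of chemotherapy, type of cancer, gender, and age". The value of the outcome at T0 does not appear there. The section does not say whether the response is the follow-up value or the change from T0.

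The same five covariates appear under sample size estimation for the Cox model of incident neuropathy. In that model there is no baseline outcome to include, because patients with pre-existing neuropathy are excluded.

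The T0 data will exist. Under experimental design, "The baseline assessment (T0) is performed prior to the first cycle of chemotherapy". Table 1 marks neuroelectrography, the row "Static and dynamic postural control" and the whole questionnaire block (FACT/GOG-Ntx, CIPN20, QLQ-C30, PainDETECT with VAS, FFKA) at T0 and again at T1, Tp, T2 and Ti.

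**The concern.** A list that suits a time-to-event endpoint without a baseline value has been carried over to endpoints that have one. The T0 value is often the best single predictor of a later value of the same measure. Leaving it out keeps between-patient variation in the error term that could be removed. The t-test named alongside the regression does not remove it either, if it is applied to follow-up values.

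The design does not make up for this. Minimisation balances study centre and type of chemotherapy only, so chance differences between arms in T0 sway, nerve amplitude, quality of life or activity are neither balanced directly nor adjusted for. At stake are the width of the confidence intervals and the power for the secondary endpoints.

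**Working it through.** The protocol states no SD, detectable difference, power or correlation for any continuous secondary endpoint, so there is no figure of its own to reproduce.

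**Inputs**
- 65 evaluable patients per arm, two-sided alpha 0.05: from the sample size section, where they are stated for the primary endpoint.
- r, the baseline–follow-up correlation left after the five listed covariates: assumed, 0.3 to 0.7.
- True difference between one intervention and control of 0.4 SD: assumed. SD is that of the follow-up value after the listed covariates.

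**Residual variance.** Adding T0 multiplies the variance by 1 − r². The effective size per arm is 65/(1 − r²). Power is Φ(0.4·√(65/2)/√(1 − r²) − 1.96), where 0.4·√32.5 = 2.280.

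| r | Variance removed | CI width factor √(1 − r²) | Acts like n per arm | Power at 0.4 SD |
|---|---|---|---|---|
| no T0 term | 0% | 1.00 | 65 | Φ(2.280 − 1.96) = 63% |
| 0.3 | 9% | 0.95 | 65/0.91 = 71 | Φ(2.280/0.954 − 1.96) = 67% |
| 0.5 | 25% | 0.87 | 65/0.75 = 87 | Φ(2.280/0.866 − 1.96) = 75% |
| 0.7 | 49% | 0.71 | 65/0.51 = 127 | Φ(2.280/0.714 − 1.96) = 89% |

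**Detectable difference.** With 80% power it is (1.96 + 0.842)·√(2/65) = 0.49 SD without T0. Multiplied by the width factor it becomes 0.47, 0.43 and 0.35 SD at r = 0.3, 0.5 and 0.7. This version needs no assumed effect.

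**If all 79 recruited per arm were analysed.** Power at 0.4 SD would be 71% without T0, and 75%, 83% and 94% at the same three values of r.

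**If change scores were intended.** With equal SDs at both times, a change score has relative variance 2(1 − r), against 1 − r² for the T0-adjusted model:

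| r | Change score | T0-adjusted |
|---|---|---|
| 0.3 | 1.40 | 0.91 |
| 0.5 | 1.00 | 0.75 |
| 0.7 | 0.60 | 0.51 |

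At r = 0.7 the change score already gives Φ(2.280/√0.60 − 1.96) = 84%, so adjustment adds about 5 points, not 26. At r = 0.5 the change score does no better than the follow-up value alone, and the gain remains 63% to 75%.

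**The case against.** The strongest reply is that the response variable is not stated. A condensed article may leave that to the analysis plan, and the mention of Wilcoxon signed-rank tests, a paired procedure, hints at some comparison with T0. The covariate sentence is also generic and does not say that nothing else may enter. This stands in part: the text does not show a deliberate decision to exclude T0, and the gain is smaller at high r if change scores were meant. It does not remove the point. The list is written out, the T0 value is not on it, and adjustment has the lower variance under either reading.

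The second reply concerns size. Both r and the 0.4 SD difference are assumed, and for some endpoints r may be low. The eligibility text says "Exclusion criteria is a pre-existing neuropathy of other cause", previous neurotoxic therapy is excluded as well, and T0 precedes chemotherapy. Neuropathy symptom and neuropathic pain scores may therefore cluster near the floor at T0 and predict little. This stands, and it is why the range starts at 0.3.

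A reader might also infer that the missing-data handling is at fault, because complete-case analyses carry the intention-to-treat label. The same sentence meets most of this: "Intention-to-treat analyses will be conducted based on complete cases and on multiply imputed data". Which result leads is a matter an analysis plan commonly settles, and it is not part of this point.

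**Conclusion.** The point holds as a matter of efficiency for the continuous secondary endpoints measured at T0. Across assumed r of 0.3 to 0.7, including T0 removes 9% to 49% of residual variance. At 65 per arm and an assumed 0.4 SD, power rises from 63% to between 67% and 89%. The lower end is the better guide for neuropathy symptom and neuropathic pain scores. Nerve conduction, sway path, quality of life and physical activity are likely to gain more. The documents contain nothing that would narrow the range.

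A reader might infer that the planned comparisons are biased, or that the main trial result is affected. Neither follows. Randomisation keeps the comparison unbiased without T0; what is lost is precision and the correction of chance imbalance. The log-rank and Cox analyses of incident neuropathy have no baseline outcome to adjust for and are unaffected. The change is worth making before analysis, but the analysis as written is not invalid.

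**What to change.** In the section on data management and analyses, add the T0 value of the outcome to the covariates of the linear or median regression models, for each continuous secondary endpoint measured at T0. State that this adjusted model, fitted at each defined time point, is the main analysis, and that the unadjusted t-test is at most supportive. State also whether the response is the follow-up value or the change from T0. In a linear model with T0 as covariate the estimated treatment effect is the same either way.

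A mixed model over T1, Tp and T2 may look like the natural extension, but it does not fit the schedule as written. For most patients T1 and Tp are the same visit, while those treated for longer have both, so the visit structure would first have to be redefined. Adjustment at each time point avoids this.

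The cost is a sentence or two in the analysis text and one model term per endpoint. No additional visits, measurements or patients are needed.
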